#### Environmental measures

To assess the home presence and availability of 20 fruits, 14 vegetables, 11 physical activity devices, and electronics in bedrooms (e.g., televisions), a home health assessment survey [49] is administered by the patient navigator at an initial (session 5) and a follow-up (session 15) home visits. Data from these surveys are used to compare changes in the home environment associated with the intervention received by families.

### Clinical provider measure

#### Process evaluation

At the end of the intervention period, a survey will be sent to health care providers of children participating in the program. The survey will collect provider perspectives of the program and value of receiving letters listing the child’s progress, goals/objectives: 1) increased knowledge of patient’s program participation, 2) helpful or unnecessary communication, and 3) affected the patient’s weight management care in the clinical setting.

#### Patient navigator measure

##### Process evaluation

To evaluate the experience and lessons learned from patient navigators working with families, we will analyze the patient navigators’ field notes and conduct individual interview with currents and available former patient navigators.

#### Family measure

##### Process evaluation

At the end of the intervention period, focus groups will be conducted with family caregivers graduating from the program to evaluate their perceptions, program usefulness and suggestions for improvement in curriculum content and delivery.

#### Intervention fidelity

At the end of each home visit, to monitor and assure fidelity to project goals and content, patient navigators use a Likert scale to assess whether learning objectives were: 1) delivered; 2) understood; 3) family’s perceived importance of the topic; and 4) family’s confidence in making a change. Patient navigator intervention assessments are recorded on paper and then transferred to a software application. To ensure the curriculum is delivered as intended, the patient navigators record the duration of each session by noting the start and end time of each session.

### Enrollment and retention efforts

Assistance from the child’s primary care provider is sought to improve program enrollment and retention. For families who decline to participate despite previously agreeing, or families who drop-out of the program after attending some sessions, the clinician liaison contacts the child’s provider and asks for permission to send a language-concordant letter to the child’s caregiver, on behalf of the clinician, encouraging program participation or completion.

### Sample size and power

The primary outcome is BMI z-scores over time from baseline to post-intervention in treated children, and from baseline to the start of intervention in delayed intervention children. We hypothesize that compared with children receiving delayed intervention, children in the intervention group will experience greater reduction in BMI z-scores over time as shown by a greater decrease in BMI z-score slope. A sample size of 80 intervention children and a frequency matched cohort (by age category) of 160 controls will provide 81% power to detect a 0.39 effect size difference between groups.

### Statistical analysis

#### Primary analysis

To determine the effect of the program on the BMI z-score of treated children, we will compare change in BMI z-scores for treated children to change in BMI z-scores in the delayed intervention control group over an equivalent time frame using general linear mixed effects models (growth curve models) with random intercept and random slopes, adjusting for patient and family-level covariates. Covariates that differ at baseline between the intervention and delayed-control groups will be included in multivariable models.

#### Secondary analysis

To determine intervention effect on patient physical activity and eating behaviors, we will compare the mean “5-2-1-0” index from baseline to post-intervention using the paired *t*-test. Additional analyses will be carried out using general linear mixed models with repeated measures on children to adjust for covariates and explore possible baseline predictors of change.

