Research suggests that patient navigators and lay health workers can improve outcomes for chronic disease in adults [18–20] and children [21] and are effective in facilitating behavior change in various settings [22]. The efficacy of home-based, childhood obesity interventions to reduce children’s body mass index (BMI) is unknown [15, 23]. The home-based model is unique by providing an opportunity to observe and intervene with the home food and activity environment [13, 15, 23, 24]. In addition, family-based obesity interventions involving the child and the parent are associated with positive outcomes since families treated together share common treatment goals [25–27]. When the caregiver is included in obesity management programs [28, 29], families have demonstrated changed behaviors; intensive lifestyle and parenting skills education has resulted in sustained weight loss [30–33].

The Community Outreach Obesity Prevention Trial (COOPT) is an ongoing, 4-year (October 2011-September 2015) randomized controlled trial that tests the effectiveness of a home-based patient navigator program delivered to preschoolers of a large urban safety-net health care system. The intervention targets children aged 2–5 years within a predominantly Latino population. The primary goals are to examine the effect of the intervention in reducing the BMI z-score in the patient and the changes in health behaviors using the “5-2-1-0” daily targets (i.e., 5 fruits and vegetables, less than 2 hours screen time, 1 hour or more of exercise and 0 sweetened drinks) [34] using a home-based, patient navigator-mediated childhood obesity intervention.

COOPT is delivered by patient navigators at a family’s home. By focusing the program on the family unit, the parent sets goals for the child taking into account family dynamics around nutrition and physical activities. Primary care providers often lack the time to offer intensive weight counseling to families since the average well child visit is less than 20 minutes [35], and many providers do not feel they have the tools or knowledge to provide adequate weight management counseling [36, 37]. This intensive 25-hour program provides [38] a home-based platform for patient navigators to offer hands-on opportunities for skill-building, provide detailed education and counseling to families, reinforce learned concepts throughout the intervention, and offer opportunities for families to set, evaluate, and modify goals, as necessary.

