**Fig. 1 Fig1:**
[figure not shown]
Flow of Children into the Study: Randomization, Recruitment, Enrollment, and Intervention Processes, Denver Health, 2012-2015

The primary outcome measure is BMI z-score over time in children receiving the intervention compared to waitlist controls (delayed intervention). We hypothesize that children receiving the intervention will have a greater reduction in BMI z-scores than children in the waitlist control group. We will compare the change in BMI z-score slope of the two groups from baseline to follow-up period. The follow-up period of the intervention group is from the start through the end of the intervention. The follow-up period for the delayed intervention group is from recruitment to the start of the intervention.

The secondary outcome is change in health behaviors using the “5-2-1-0” daily targets (i.e., 5 fruits and vegetables, less than 2 hours screen time, 1 hour or more of exercise, and 0 sweetened drinks). We hypothesize that children receiving the intervention will experience a greater improvement in “5-2-1-0” measures from baseline to post-intervention compared with children in control group. A thorough evaluation of the delivery processes and acceptance by stakeholders will inform the potential for implementation and dissemination of the intervention.

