### Recruitment and randomization

Participant recruitment is performed from a randomized list of overweight or obese patients who had a BMI measure recorded at least 9 months prior to study initiation (Fig. 1). Biologically implausible values for height or weight are excluded using a CDC-developed algorithm [40]. A research assistant contacts potential enrollees from the randomized list. Prior to the call, families are mailed a postcard with a brief description of the program and informed that they will soon be contacted. Once called, a bilingual English-Spanish research assistant explains the study to the family over the phone. If the family agrees to participate, the research assistant reads a verbal consent and documents consent. After oral consent is obtained, a baseline set of behavioral questions is administered. The survey is re-administered if more than 30 days have lapsed between the administration of the baseline survey and the start of the intervention. These baseline pre-intervention behaviors are compared with post-intervention and 6-month post-intervention behaviors recorded on subsequent questionnaires.

Study participants are told they will be scheduled to begin patient navigator visits in a staggered manner, using a stepped-wedge design [41] with individuals assigned to an intervention cohort to start the intervention. Those not enrolled in the initial intervention cohort are sent quarterly newsletters with information and resources unrelated to the intervention to keep participants connected to the study, during the delayed period.

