##### Diet and physical activity

The physical activity and eating behaviors of the child as summarized in “5-2-1-0” daily targets are captured by a standard survey [48] administered to the child’s caregiver at the time of recruitment, at the completion of the intervention and at 6-months post-intervention. Families receive a 10 dollar gift card for each completed survey.

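### The 5-2-1-0 hypothesis is stated against the control group, but the only test named is a within-child paired t-test, which cannot test it

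*Protocol article*

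**What the plan says.** Under Overview and hypotheses, the behavioural hypothesis is a between-group one: intervention children are expected to improve more on 5-2-1-0 "measures from baseline to post-intervention compared with children in control group".

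Under Secondary analysis, the aim is causal and the test is one-group. The text begins "To determine intervention effect on patient physical activity and eating behaviors, we will compare the mean" and then takes the 5-2-1-0 "index from baseline to post-intervention using the paired" t-test. Further analyses are planned as "general linear mixed models with repeated measures on children to adjust for covariates and explore possible baseline predictors of change".

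Two sections describe when the survey is given:

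- **Recruitment and randomization:** "The survey is re-administered if more than 30 days have lapsed between the administration of the baseline survey and the start of the intervention". It continues: "These baseline pre-intervention behaviors are compared with post-intervention and 6-month post-intervention behaviors recorded on subsequent questionnaires".
- **Diet and physical activity:** the caregiver survey is given "at the time of recruitment, at the completion of the intervention and at 6-months post-intervention". No survey just before the start of a delayed intervention is listed.

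By contrast, the Primary analysis section sets change in BMI z-score in treated children against change in the delayed-intervention controls over an equivalent time frame.

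**The concern.** A paired t-test asks whether the mean within-child change differs from zero. The hypothesis asks whether change in treated children exceeds change in untreated children. These are different questions, and no result from the first settles the second.

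The outcome is caregiver-reported, in children aged 2 to 5, and is asked again after months. Season, the child's growing older and repeated asking could each move the answers without any programme effect. A before-after test counts all such movement as benefit. A trial that presents itself as randomised and controlled would then report a behavioural effect with no control behind it. This outcome is one of only two for which the article states a comparative hypothesis.

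**Working it through.** **1. Hypothesis and analysis side by side**

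| Item | Section | Contrast |
|---|---|---|
| BMI z-score hypothesis | Overview and hypotheses | Treated vs waitlist |
| BMI z-score analysis | Primary analysis | Treated change vs delayed-group change |
| 5-2-1-0 hypothesis | Overview and hypotheses | Treated vs control |
| 5-2-1-0 test | Secondary analysis | Before vs after, within child |
| 5-2-1-0 additional models | Secondary analysis | Covariates and predictors; no group contrast named |

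Hypothesis and analysis match for BMI z-score. They do not match for 5-2-1-0.

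**2. The plan's own power figure**

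Sample size and power gives 80 intervention children, 160 controls, effect size 0.39 and 81% power, for the BMI z-score. Alpha is not stated; two-sided 0.05 is assumed.

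- Standard error in SD units: √(1/80 + 1/160) = √0.01875 = 0.137
- Noncentrality: 0.39 / 0.137 = 2.85
- Power: 81.3% by the normal approximation, 81.0% by the noncentral t with 238 df

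The figure reproduces (a one-sided 0.05 test would give about 89%). No figure is given for the behavioural outcome.

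**3. What drift does to the paired test**

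Suppose the programme has no effect and the index improves by d SD of the change score for other reasons. The paired t statistic then has noncentrality d√n with n − 1 df. Take n = 80, borrowed from the BMI calculation, and two-sided 0.05. The article gives neither d nor n for this test.

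| d (assumed) | d√80 | Probability of rejection |
|---|---|---|
| 0 | 0 | 5% |
| 0.1 | 0.89 | 14% |
| 0.2 | 1.79 | 42% |
| 0.3 | 2.68 | 76% |

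For d above zero, nearly all of these rejections are in the direction of improvement.

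**4. The same drift in a between-group contrast**

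If the drift is common to both groups over comparable intervals, it cancels in the difference of changes and the error rate stays at 5%. The price is precision. In SD-of-change units the standard error is 0.137 (80 vs 160) against 1/√80 = 0.112 for the paired change. The ratio is √1.5 = 1.22, so the interval is about 22% wider. This assumes that all 160 controls contribute an untreated change and that the two sets of changes are independent.

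**The case against.** The strongest reply is that this is a condensed article about a secondary outcome, and that exact model terms are commonly left to an analysis plan. The additional mixed models belong to the same family as the controlled primary model, and nothing excludes a group term. A reader might infer that the plan throws the randomised waitlist away altogether for this outcome; the text does not go that far. What stands against the reply is that the article does not leave the test open. It names one, and that test does not fit the hypothesis. The mixed models are called additional and are given a different purpose.

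A second reply is that the control data may not be there. A reader might infer from the repeat survey that untreated change is already being collected and that only wording needs to change. The documents do not support that. The repeat is conditional on more than 30 days having passed, it reads as a refresh of a stale baseline, and the Diet and physical activity schedule omits it. This objection stands and shapes the fix.

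Third, the intervals may differ. The Abstract describes five 6-month engagements, so the wait from recruitment to the repeat survey could run from just over 30 days to many months. That range is inferred, since no distribution is given. A crude comparison would let season and age back in. This also stands.

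Finally, the Background places the behaviours under the trial's primary goals ("The primary goals are to examine the effect of the intervention in reducing the BMI z-score in the patient", followed by the 5-2-1-0 changes). A reader might infer a conflict over which outcome is primary. That is loose background prose: the sections on hypotheses, outcome measures and sample size all make BMI z-score the primary outcome.

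**Conclusion.** The mismatch is on the face of the document and holds. The named test of the 5-2-1-0 outcome cannot support or refute a hypothesis framed against controls, and it attributes any change over time to the programme.

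The 14%, 42% and 76% show how a before-after test behaves under drift. They do not estimate the error in this trial, because the drift values, n = 80 and two-sided 0.05 are all assumptions. At a given drift the rate would be higher with more treated children in the test, but the article gives no number for it.

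The primary BMI z-score analysis is explicitly controlled and untouched. Severity: should-fix.

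**What to change.** 1. **Name the controlled contrast as the main secondary test.** Compare treated change (last pre-intervention survey to completion survey) with delayed-group change (recruitment survey to the repeat survey before the start of the intervention), over an equivalent time frame, as the Primary analysis section already requires for BMI z-score. Use a mixed model with repeated measures on the child and a group-by-time term that accounts for differing survey intervals and calendar time. The published primary model mentions no calendar-time adjustment, so this must be written out here and not borrowed by reference.
2. **Keep the paired change as description only**, and do not call it the intervention effect.
3. **Reconcile the survey schedule.** Bring Diet and physical activity into line with Recruitment and randomization, so that the survey before a delayed start is a scheduled assessment and the control-period data are secured.

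Cost: mainly analysis wording, provided the repeat survey is in fact carried out. The interval will be wider than for the paired test, by about 22% under the assumptions above. Children who start within 30 days of their baseline survey contribute no control-period change. The contrast removes drift common to both groups, but not reporting bias that arises because treated families are coached on these same targets; that should be stated as a limitation.

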## Discussion

The need for robust childhood obesity interventions is evident for preschoolers, but limited current availability and capacity for comprehensive childhood obesity management mean many children have unmet service needs. Primary care providers ideally would provide counseling for families with overweight and obese children, but clinicians have: 1) competing demands, 2) limited time, knowledge and resources, and 3) lack of in-depth nutrition and physical activities counseling skills. Culturally competent patient navigators trained in supporting lifestyle change may be an effective adjunct to clinically-based obesity management services for preschoolers. They provide in-depth counseling around nutrition and physical activities to families.

**Table 2 Tab2:** Environmental observations to assess in-home family chaos [50]

Environmental observation	Yes	No
TV on		
Music on		
More than one person talking at a time		
Cluttered rooms, making it difficult to walk around or meet for home visit		
More than family present in the home		
Non-compliance to parent directions (ignored or refused by child)		
Disrespectful language		
Inappropriate behavior between 2 people		
Answering the phone (texting) during visit		

Our study, The Community Outreach Obesity Prevention Trial (COOPT) is a randomized controlled trial testing a family-centered obesity treatment in a predominantly Latino population of preschool age children. This childhood obesity management program is delivered by patient navigators in a home setting. Patient navigators have a unique opportunity to develop a trusting relationship with families over a detailed 16-session curriculum around nutrition, physical exercises, and parenting skills, to assess the home food/exercise device environment, and to offer healthy recommendations for the families.

The study targets a low-income population who often experience social and environmental obstacles precluding a caregiver’s ability to make healthy changes for their child. For families with limited budget, the patient navigators work with the families to choose alternative healthy and affordable foods. When family and environmental chaos (Table 2 [50]) is observed during home visits, the patient navigators have the opportunity to address them with the families or to provide resources to assist the families. At the end of each session, the patient navigators assess the parent’s level of understanding of the session, the importance of the topic, and their confidence in making the proposed changes. At three points during the program (i.e., first session, mid-intervention, and last session), patient navigators assess parental readiness for change. Assessments at the end of each session, in conjunction with parental readiness to change, guide patient navigators to develop goals and objectives tailored to individual families’ needs and more likely to be achieved.

The study is innovative in its focus on preschool-aged, Latino children from low-income families; this population has not been typically targeted in obesity management programs. The study is also novel in the home-based intervention venue, which provides rich data about acceptance and characterization of barriers and facilitators of healthy change within the home. The home-based intervention links to clinical care through update/outcome letters and program impact assessments shared with medical providers. By informing primary care providers about a child’s program accomplishments and challenges, the clinician may personalize messages with families during subsequent clinical visits.

## Abbreviations

BMI: Body Mass Index
COOPT: Community Outreach Obesity Prevention Trial
USPTF: US Preventive Services Task Force
